### The mediterranean diet

Participants allocated to the intervention group will undergo six individual nutritional appointments, where they will receive individual counselling aiming to promote adherence to the MedDiet.

The MedDiet components promoted in nutritional appointments will follow a similar approach to the one used in the PREDIMED trial [27]. The nutritional counselling will not focus on calorie management or weight change and will be tailored to each participant’s dietary routines and preferences.

The intervention will contemplate the following recommendations:

#### Positive recommendations

Use of olive oil as main fat, both for cooking and dressing;Consumption of two or more servings of vegetables daily (200 g of vegetables per serving);Consumption of 2–3 servings of fresh fruits per day;Intake of 3 or more servings of legumes per week;Consumption of 3 or more servings of fish per week (100–150 g of fish per serving or 200 g of shellfish);Consumption of 3 or more servings of nuts a week (30 g of nuts per serving);Meat consumption mainly from poultry (without skin) or rabbit;Homemade cooked meals with tomato, garlic, and onion, at least twice a week;

#### Negative recommendation

*Eliminate or drastically reduce the following foods*:

Cream, butter, and margarine;Cold meats, pâtés, and duck meat;Carbonated and/or sugared beverages;Pastries and industrial baked products (cakes, doughnuts, or cookies);Industrial deserts;French fries and potato chips;Pre-cooked cakes and sweets;Alcohol should be limited to 300ml of wine per day (150 cc at meals for men and 100 cc for women, during meals).

Due to the recognized risk of interactions between alcohol and antidepressant medication [28], participants will be advised to completely avoid alcohol consumption. The recommendation to restrict the consumption of alcohol will only be given if participants report already including alcohol in their diets.

Training for nutritionists delivering the intervention will be provided prior to the beginning of recruitment, namely in MDD, trauma, therapeutic relationship, and in MedDiet. Additional training will be provided during the duration of the trial. This training will consider doubts and/or difficulties reported by the intervention team during the nutritional counselling as well as other topics considered relevant to promote adherence to MedDiet.

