#### Inclusion criteria

Aged between 18 and 70 years old;Able to understand and provide informed consent;Able to read and write;Have a diagnosis of MDD (according to the International Classification of Diseases Version 10 F32.0; F32.1; F32.2 criteria).Score on the Beck Depression Inventory-II scale (BDI-II) > 13;Elevated biomarkers of inflammation (CRP ≥ 3 mg/l or IL-6 > 1.8pg/ml) [25];Able to eat a MedDiet without impeditive physical limitations, allergies, or intolerances;Treated with the first antidepressant prescribed for at least 4 weeks [26].

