### Intervention

Participants randomly allocated to the intervention group will attend six nutrition appointments with a duration between 30 and 60 min, in one of the participating centres of the trial, performed by a registered nutritionist in weeks 1, 2, 4, 6, 8 and 10. The intervention will promote adherence to the MedDiet without specific recommendations for weight change or calorie intake control.

Registered nutritionists involved in the intervention will participate in the baseline assessment but not in data collection at 12 weeks or at any of the follow-up assessments.

Both groups will maintain the TAU for MDD.

This trial will use a passive control group, with no active intervention apart from TAU.

All participants will have to be medicated with an antidepressant at the beginning of the trial. Changes in pharmacotherapy, including medicines and/or dosages, and additional treatments provided to participants (e.g., psychotherapy) will be documented and taken into consideration during statistical analysis.

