## Smoking and drinking habits

Smoking and drinking habits will be assed using a customized survey instrument.

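### The intervention's recommendation list keeps a daily wine limit of 300 ml, the next paragraph advises full abstinence, and the text never says that one replaces the other

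*Protocol article*

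**What the plan says.** All references are to the protocol article.

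- The section The mediterranean diet introduces the two lists that follow with "The intervention will contemplate the following recommendations". It also says that the approach resembles the one used in an earlier Mediterranean diet trial. No item is marked as belonging to that trial only.
- The list under Negative recommendation covers foods to be cut out or sharply cut down. Its last item reads "Alcohol should be limited to 300ml of wine per day", with per-meal amounts in brackets: "150 cc at meals for men and 100 cc for women, during meals".
- The paragraph after the list cites interactions between alcohol and antidepressants and states that "participants will be advised to completely avoid alcohol consumption".
- The same paragraph closes with "The recommendation to restrict the consumption of alcohol will only be given if participants report already including alcohol in their diets".
- Inclusion criteria requires "Treated with the first antidepressant prescribed for at least 4 weeks", and Intervention adds "All participants will have to be medicated with an antidepressant at the beginning of the trial".

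**The concern.** The same section gives two different alcohol instructions for the same people. The list sets a ceiling above zero. The paragraph below sets the target at zero, for a reason that covers every participant at entry. No linking word tells the reader that the second instruction overrides the first.

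Two things are at stake:

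- **Safety.** A nutritionist counselling from the list could tell a drinker on an antidepressant that some wine each day is acceptable, which the protocol's own rationale rules out.
- **Consistent delivery.** Counselling is given by nutritionists at several centres. If some apply the limit and others apply abstinence, drinkers in the intervention arm receive different advice.

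**Working it through.** No statistical figure depends on this point, so the check is a comparison of the texts. A short calculation then sizes the gap between the two instructions.

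**1. Is the wine limit part of this intervention?** Yes. The introductory sentence in The mediterranean diet presents the lists as what the intervention recommends. The resemblance to an earlier trial is a remark about approach. It does not set the wine item apart from the other items.

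**2. Does a group exist at entry for whom the limit is the right instruction?** No. The reason given for abstinence is antidepressant treatment. Inclusion criteria and Intervention both make that treatment a condition of entry, so the reason applies to everyone. The article does not say that the limit is kept for participants who later stop their medication.

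**3. Does the closing sentence settle the matter?** Not fully. It says to whom the advice to restrict alcohol is given: current drinkers.

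- *Reading A:* restricting means the abstinence advice just stated. This is the more natural reading. Drinkers are told to stop, and the list item has no role.
- *Reading B:* restricting means the limit in the list, because that is the only item worded as a limit. Drinkers would then be given the wine limit, against the sentence immediately before.

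On either reading the sentence is addressed to current drinkers, and for them the target cannot be both zero and up to 300 ml a day.

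**4. How far apart are the two instructions?** The inputs are the 300 ml daily figure and the 150 cc and 100 cc per-meal figures, all from the list item. The number of meals with wine per day is not given, so a range of 1 to 3 is assumed. The abstinence target is 0 ml, so the gap equals the permitted amount:

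daily gap = min(per-meal amount × meals, 300 ml); weekly gap = 7 × daily gap

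| Meals with wine per day (assumed) | Men, daily | Men, weekly | Women, daily | Women, weekly |
|---|---|---|---|---|
| 1 | 150 ml | 1.05 L | 100 ml | 0.7 L |
| 2 | 300 ml | 2.1 L | 200 ml | 1.4 L |
| 3 | 450 ml, capped at 300 ml | 2.1 L | 300 ml | 2.1 L |

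At two meals a day, the daily total matches the per-meal figure for men only. The line is therefore also unclear in itself. This is a side observation, and the contradiction does not depend on it.

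**5. How many participants could be affected?** Only drinkers in the intervention arm. The article gives no share of drinkers. The ceiling is the planned arm size of 95 (section Sample size).

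**The case against.** The strongest reply is that the text resolves the conflict where it arises. A general list borrowed from an earlier diet trial is followed at once by a paragraph that names alcohol, gives a trial-specific reason and prescribes abstinence. The last sentence then confines the advice to people who drink. Read together, these give one workable rule, which is the rule proposed below. The list item is also a ceiling under a heading about cutting down and does not recommend drinking, so a participant who abstains complies with both statements. Harm would require a nutritionist to use the list and ignore the paragraph beneath it. Training is planned before recruitment and during the trial, and an article need not reproduce the counselling materials.

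Much of this stands. Abstinence is very likely the intent, the harm is hypothetical, and training may well prevent it. The millilitre figures rest on an assumed number of meals and only illustrate the gap.

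Three things remain:

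- A ceiling of 300 ml tells a drinker that amounts below it are acceptable. That differs from telling the same person not to drink, even though an abstainer satisfies both.
- The training topics named in the article are depression, trauma, the therapeutic relationship and the diet itself. The alcohol rule is not among them, and teaching the diet from the printed list could repeat the wine line.
- Nothing is alleged to be missing through condensation. Both instructions are printed, and they conflict.

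**Conclusion.** The concern holds. The intervention text contains a wine limit and an abstinence instruction for the same medicated participants and does not say which applies. That the two conflict follows from the wording alone and needs no assumption.

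The consequence is narrow. It affects drinkers in the intervention arm: an unknown number, at most the 95 planned. Under the assumed 1 to 3 meals with wine per day, the two instructions differ by 150 to 300 ml a day for men and 100 to 300 ml for women. Harm has not been shown. Sample size, power and the primary analysis do not change. The text should be corrected because the point touches participant safety and the remedy is almost free.

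**What to change.** Delete the wine item, with its per-meal amounts, from the list under Negative recommendation. Alternatively, keep it with a note that it does not apply in this trial. Replace the last two sentences on alcohol with one rule, for example: participants who report drinking alcohol are advised to stop completely while they take antidepressants; the subject is not raised with participants who do not drink.

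Drinkers can be identified from information already planned: "Smoking and drinking habits will be assed using a customized survey instrument", with baseline as the first time point. Include the rule in the initial and continuing nutritionist training. The correction is the same on either reading of the closing sentence.

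The cost is one line removed or annotated, one passage reworded, one item added to the training, and an update to the trial register, as the section Clinical trial register provides for protocol changes. No new data, visits, participants or analyses are needed.

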**Fig. 1 Fig1:**
[figure not shown]
Recruitment and flowdiagram

## Data collection and outcomes

### Main outcome: symptoms of depression

Symptoms of depression will be assessed with the self-administered Beck Depression Inventory-II (BDI-II) [28] scale, which is a 21 item self-report instrument for measuring the severity of depression in adults and adolescents. The total score is the sum of scores on the 21 items, ranging from 0 to 63. The adequate validity and reliability of this measure [29, 30] and its ability assessing depressive symptoms and monitoring the efficacy of treatment [30] makes it a valuable instrument for the current study. The Portuguese version of the BDI-II [30] will be administered. This version presents adequate internal consistency and convergent validity.

To measure changes in the main outcome, the score of the BDI-II will be used categorically, considering the cut-offs proposed by Beck et al. (1996) 0–13 minimal depression; 14–19 mild depression; 20–28 moderate depression; 29–63 severe depression [31].

The success measure will be a decrease in category in the severity of depressive symptoms.

The analysis of the score of the BDI-II will also be performed using the scale score as a continuous variable.

#### Time frame

Baseline, 12 weeks, 6 months, 12 months.

### Specific outcomes

#### Adherence to the MedDiet

Will be assessed by the Portuguese version of the 14-point Mediterranean Diet Adherence Screener [32, 33]. This instrument evaluates the intake of foods typical of MedDiet [33]. Changes between baseline and subsequent assessments will be analysed using the score of the scale as a continuous variable.

##### Time frame

Baseline, 12 weeks, 6 months, 12 months.

#### Changes in inflammation biomarkers (CRP and IL-6)

IL-6 and CRP concentrations in blood will be measured using an Atellica CH Analyzer, between baseline and other moments of assessment.

##### Time frame

Baseline, 12 weeks, 6 months, 12 months.

#### Health-related quality of life

Will be accessed with the World Health Organization Quality of Life – Brief (WHOQOL-BREF), a 26-item short version of the more extensive WHOQOL-100 [34]. Changes in Health-related quality of life will be measured, between baseline and other moments of assessment using the score of the WHOQOL-BREF as a continuous variable.

##### Time frame

Baseline, 12 weeks, 6 months, 12 months.

#### Economic costs associated with MDD

To conduct the economic cost analysis of the intervention self-reported information will be obtained for the following variables: health care resource use (medicines, appointments, hospital admissions and other unspecified healthcare services) and employment status (occupation, current employment situation, workplace absenteeism and presenteeism). The estimation of costs associated with MDD will be calculated for healthcare resource use and the indirect costs to patients.

##### Time frame

Baseline, 12 weeks, 6 months, 12 months.

## Co-variables

### Sociodemographic variables

Sex, age, level of education, household composition, professional occupation, and nationality.

#### Time frame

Baseline.

## Medical history

Self-reported medical diagnosis, medication, self-reported allergies and food intolerances.

### Time frame

Baseline.

## Thyroid function

Thyroid-stimulating hormone (TSH), Free Thyroxine (fT4) will be measured using Atellica IM Analyzer.

### Time frame

Baseline.

## Lifestyle variables

### Physical activity

Physical activity will be assessed with the self-administered Portuguese version of the International Physical Activity Questionnaire – Short Form (IPAC-SF) [35].

#### Time frame

Baseline, 12 weeks, 6 months, 12 months.

## Smoking and drinking habits

Smoking and drinking habits will be assed using a customized survey instrument.

### Time frame

Baseline, 12 weeks, 6 months, 12 months.

### Anthropometric measurements

#### Weight, height, Body Mass Index.

Anthropometric measurements will be performed at the end of data collection by a professional not involved in the intervention. Weight will be measured using a scale DIGITAL SECA 813 and height will be assessed with a stadiometer SECA 213.

##### Time frame

Baseline, 12 weeks, 6 months, 12 months.

## Liver function

Alanine aminotransferase (ALT), Aspartate transaminase (AST), Gamaglutamil Transpeptidase (GGT) will be measured using Atellica CH Analyzer.

### Time frame

Baseline, 12 weeks, 6 months, 12 months.

## Blood cells

Hemogram and leukogram will be measured using Coulter System DxH 800.

### Time frame

Baseline, 12 weeks, 6 months, 12 months.

## Glucose metabolism

Hemoglobin A1C (HbA1C) will be measure using Bio-Rad D-100™.

### Time frame

Baseline, 12 weeks, 6 months, 12 months.

Detailed information regarding blood work analyses is described in Table 1.

**Table 1 Tab1:** Information about blood work analysis

Biomarker	Test name	Product Name	Systems	Measurement interval
Hemogram	Hemogram	Coulter	System DxH 800 Coulter	NA
Leukogram	Leukogram	Coulter	System DxH 800 Coulter	NA
hs-CRP	wrCRP	Atellica CH wrCRP	Atellica CH Analyzer	0,050–15,600 mg/dl (0,50–156,00 mg/l)
IL-6	IL-6	Atellica IM IL6	Atellica IM Analyzer	2,7–5500,0 pg/ml
ALT	ALT	Atellica CH ALT	Atellica CH Analyzer	7–1100 U/l
AST	AST	Atellica CH AST	Atellica CH Analyzer	8–1000 U/l
GGT	GGT	Atellica CH GGT	Atellica CH Analyzer	7–1200 U/l
FT4	FT4	Atellica IM FT4	Atellica IM Analyzer	0,1–12,0 ng/dl (1,3–154,8 pmol/l)
TSH	TSH3‑UL	Atellica IM TSH3‑UL	Atellica IM Analyzer	0,008–150,000 µIU/ml (mIU/l)
HbA1c	HbA1c	D-100TM HbA1c	Bio-Rad D-100™	NA

### Consent, confidentiality and data access

Only individuals who have provided written informed consent will be enrolled in the study. Participants will be informed of their right to withdraw from the study at any time without providing justification and will be assured that their decision will not have any negative impact on the provision of their normal healthcare services. Only their names and other sensitive identifying information will be stored in a physical format to protect participant privacy. Participants will be granted the right to access their data upon request.

### Discontinuation of participation and missing data

Participant’ discontinuation is expected to occur in the following scenarios: hospitalization during the trial, development of conditions that restrict adherence to the MedDiet, diagnosis of a disease that is incompatible with the intervention, or initiation of another nutritional intervention. Baseline data from participants who are excluded after baseline assessment will be included in the sample characterisation.

Missing data from participants that don’t complete all the steps planned in the trial will be analysed following an intention-to-treat (ITT) approach.

Motives of participant exclusion or abandonment will be documented and reported if the information is available.

Due to the nature of the intervention, the promoting adherence to the MedDiet, negative reactions are not expected.

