### Sample size

Considering a two-sided significance level of 5% and a power of 80% and using data from the trial published by Jacka et al. [24], the minimum sample size required to detect a difference of 20% points in the proportions of participants with a decrease in the severity of depressive symptoms, between control and intervention groups (8 and 28%, respectively), after 12 weeks, is 114 participants (57 per arm). Such difference corresponds to an odds ratio of 4.5, considered clinically relevant and smaller than the effect size derived from the SMILES trial [24]. Taking into consideration an attrition of 40% at the end of the intervention, the minimum sample size estimated is 190 (95 per arm). Estimating a prevalence of elevated inflammation in 30% of MDD patients and 10% of patients that don’t meet other inclusion criteria, the number of recruited participants estimated is 700 [2, 9].

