### Statistical analysis

Data analysis and reporting will be performed in accordance with CONSORT guidelines.

Analysis of the primary outcome will include all randomized participants, following an ITT approach.

Baseline characteristics, by group, will be reported using descriptive statistics and compared by χ2 and t-test for independent samples (or equivalent non-parametric test). To evaluate the effectiveness of the intervention, the proportion of participants with a decrease in depression severity symptoms category according to the BDI-II (main outcome) will be compared between control and intervention groups using generalised linear mixed models.

Further adjustment for relevant covariates, as supportive analysis, will be made. Secondary analyses include between-group differences over time in symptoms of depression, considering the BDI-II as a continuous variable. Regarding specific objectives, the analysis of symptoms of depression (BDI-II scale score) given the levels of CRP and IL-6 will be conducted using linear mixed models, adjusted for age, BMI, hemoglobin HbA1C, medication, physical activity, smoking and drinking habits and sex. The same method will be applied to test the effect of adherence to MedDiet on the levels of the biomarkers (CRP and IL-6) and in health-related quality of life. The association between adherence to MedDiet and changes in symptoms of depression will also be investigated, using, for this purpose, generalized linear mixed models. The economic cost-effectiveness of dietary counselling as an adjuvant treatment for MDD, compared to the usual treatment, will be presented as an incremental cost-effectiveness ratio, given the differences in the total costs of each treatment and their health effects (i.e., the proportion of patients with improvement in symptoms of depression after 12 weeks of intervention). For each outcome, results for either intervention and control group, and estimates of effect size with a 95% confidence interval will be reported. All analyses will be performed assuming a significance level of 5%.

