### Discontinuation of participation and missing data

Participants discontinuation is expected to occur in the following scenarios: hospitalization during the trial, development of conditions that forbid adherence to the MedDiet, diagnosis of a disease that is incompatible with the intervention, or initiation of another nutritional intervention. Baseline data from participants who are excluded after baseline assessment will be included in the sample characterisation.

Missing data from participants that don’t complete all the steps planned in the trial will be analysed following an ITT approach.

Motives of participant exclusion or abandonment will be documented and reported if the information is available.

Due to the nature of the intervention, the promoting adherence to the MedDiet, negative reactions are not expected.

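### The discontinuation rule ends participation, not only counselling, after events such as hospitalisation and does not say that outcomes are still collected, which sits badly with the promised ITT analysis and the costing of admissions

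*Protocol article*

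**What the plan says.** The section headed Discontinuation of participation and missing data appears twice in the protocol article: once after the consent and data-access section, and again after the section on benefits, risks and compensation. The heading concerns participation in the trial, not attendance at counselling.

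- **Triggers, first copy:** "discontinuation is expected to occur in the following scenarios: hospitalization during the trial, development of conditions that restrict adherence to the MedDiet". The list goes on to an incompatible disease and to starting a different nutritional intervention.
- **Triggers, second copy:** the same list, except that the diet item reads "development of conditions that forbid adherence to the MedDiet".
- **Data of those excluded:** "Baseline data from participants who are excluded after baseline assessment will be included in the sample characterisation".
- **Non-completers:** "Missing data from participants that don’t complete all the steps planned in the trial will be analysed following an intention-to-treat (ITT) approach".
- **Primary analysis (Statistical analysis):** "Analysis of the primary outcome will include all randomized participants, following an ITT approach".
- **Cost items (Economic costs associated with MDD):** "health care resource use (medicines, appointments, hospital admissions and other unspecified healthcare services", collected at baseline, 12 weeks, 6 months and 12 months.

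Neither copy says whether BDI-II or resource use is still collected after one of these events.

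**The concern.** A site following the section as written would end a participant's involvement on admission to hospital and would have no instruction to obtain the 12-week BDI-II. The person remains in the ITT denominator but has no outcome. ITT settles who is analysed and in which arm; it does not supply a measurement that nobody took, and no later choice of missing-data method does so either.

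The triggers are not obviously neutral. Hospitalisation may reflect worsening depression, which is the outcome itself. Two triggers are defined by the Mediterranean diet or by the intervention, and only one arm is counselled to follow that diet. In an open-label trial, staff who know the allocation may judge those triggers differently in the two arms. Starting another diet programme might be more common among controls.

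The economic analysis has a related difficulty. Admissions are a cost component, yet an admission is also a listed reason for ending participation. If resource use is then no longer collected, costs are cut short for participants who may be among the most expensive.

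**Working it through.** **1. The texts side by side**

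| Question | Discontinuation section (both copies) | Elsewhere in the article |
|---|---|---|
| What stops? | Participation | – |
| Which data of excluded participants are named? | Baseline data, for sample characterisation | – |
| Who is in the primary analysis? | Non-completers' missing data handled by ITT | Everyone randomised (Statistical analysis) |
| Is the 12-week outcome collected after the event? | Not stated | Not stated |
| Are admissions needed as data? | Admission is a trigger | Admission is a cost item |

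The listed events read mainly as occurring after randomisation. Hospitalisation is specified as during the trial. Starting a different nutritional intervention suggests that one is already under way, and taking part in a diet intervention at entry is already an exclusion criterion.

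**2. The plan's own figures**

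Inputs from the Sample size section: 8% and 28% success, two-sided 5%, power 80%, attrition 40%. With the pooled proportion (0.08 + 0.28)/2 = 0.18:

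n per arm = [1.960·√(2·0.18·0.82) + 0.842·√(0.08·0.92 + 0.28·0.72)]² / 0.20² = (1.065 + 0.442)² / 0.04 ≈ 56.7, so 57 per arm and 114 in total.

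For attrition, 57/(1 − 0.40) = 95 per arm and 190 in total. Both stated figures reproduce. The point here does not depend on them; they supply the rates used below.

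**3. Illustration: one arm loses a fraction x, all of them failures**

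Assumptions, none of them in the protocol: the excluded leave the analysis, every one would have been a failure, and only one arm is affected. The success proportion p becomes p/(1 − x).

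| p | x = 5% | x = 10% | Share of the 20-point target |
|---|---|---|---|
| 28% | 0.28/0.95 = 29.5% (+1.5) | 0.28/0.90 = 31.1% (+3.1) | 7% to 16% |
| 8% | 0.08/0.95 = 8.4% (+0.4) | 0.08/0.90 = 8.9% (+0.9) | 2% to 4% |

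**4. Illustration: no true effect, 95 randomised per arm, unequal exclusion, all excluded are failures**

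| True success, both arms | Excluded, intervention / control | Spurious difference (points) | Two-sided type I error |
|---|---|---|---|
| 18% | 10% / 5% | 0.180/0.90 − 0.180/0.95 = +1.1 | about 5.4% |
| 18% | 15% / 5% | 0.180/0.85 − 0.180/0.95 = +2.2 | about 6.6% |
| 18% | 20% / 5% | 0.180/0.80 − 0.180/0.95 = +3.6 | about 8.8% |
| 28% | 20% / 5% | 0.280/0.80 − 0.280/0.95 = +5.5 | about 11.9% |
| any | equal | 0 | no spurious difference |

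Swapping the arms reverses the sign of the difference.

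**The case against.** The strongest reply is that the passages can be read together without conflict: participants who discontinue are described at baseline, their reasons are reported, and they stay in the ITT analysis with missing outcomes handled by a method set out elsewhere. Four stronger readings are tempting, and the documents do not support them.

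- **Excluded participants are kept only for baseline description, so the plan contradicts itself.** The sentence on baseline data says what is included; it does not say that other data are discarded. The same section applies ITT to non-completers, in agreement with the Statistical analysis section. This is a tension, not an outright contradiction.
- **An admission ends data collection.** No section says that BDI-II or resource use stops being collected. Truncated costs are a risk of following the wording, not a stated rule.
- **Cases are removed unequally by arm.** The triggers are written for all participants and no rates by arm are given. Diet-linked triggers may affect the counselled arm more and another diet programme the control arm more, so the effects could partly cancel.
- **The distortion is larger.** At an assumed 50% success rate the formula in step 3 would give 2.6 to 5.6 points, but that rate appears nowhere in the protocol, which plans on 8% and 28%.

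Timing is also not fully settled. The text says after baseline assessment, not after randomisation; thyroid function is measured at baseline and thyroid dysfunction is an exclusion, so some exclusions could precede randomisation. The flow diagram is not available here. The wording mismatch between the two copies may be purely editorial. A fuller protocol could also state that follow-up continues.

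What survives is that the published wording ends participation, uses the language of exclusion, and does not keep these people in follow-up. The ITT sentences do not repair that, because they address analysis and not collection. For the same reason it cannot simply be left to an analysis plan.

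**Conclusion.** The point holds as a tension that needs rewording. Followed literally, the discontinuation section risks losing 12-week BDI-II and cost data after events that are plausibly related to outcome (hospitalisation) or to arm (diet-linked triggers under open-label conditions), and the ITT commitment cannot restore them.

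The size and direction of any bias are unknown. The figures under working are conditional: they require that excluded participants leave the analysis and that all would have been failures. One-sided exclusion of 5 to 10% then shifts that arm by 1.5 to 3.1 points at 28% and 0.4 to 0.9 points at 8%, against a 20-point target. There is no bias if exclusion is equal and there is no true effect. The 40% attrition allowance shows that many outcomes may be missing, but the protocol does not attribute it to these triggers.

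The missing-data method itself is not criticised, since it may be set out in a document that is not shown.

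**What to change.** 1. Separate stopping the counselling from leaving the study, and define each.
2. State that, unless consent is withdrawn, BDI-II and resource use are still collected at 12 weeks, 6 months and 12 months after any of the listed events, and that everyone randomised stays in the ITT analysis.
3. Reword the sentence on baseline data so that it does not imply removal from the analysis, and say whether it refers to exclusions before or after randomisation.
4. Merge the two copies of the section into one text and reconcile *restrict* with *forbid*. Which clinical criterion applies, and when counselling stops, is for the investigators to decide.

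The cost is a wording change and modest extra follow-up effort. BDI-II is self-administered and resource use is self-reported, so no new procedure is needed. The change should be made early, because outcomes missed during the trial cannot be recovered at analysis.
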